## Abstract

**Background:**

Pregnancies complicated by abnormal umbilical artery Doppler blood flow patterns often result in the baby being born both preterm and growth-restricted. These babies are at high risk of milk intolerance and necrotising enterocolitis, as well as post-natal growth failure, and there is no clinical consensus about how best to feed them. Policies of both early milk feeding and late milk feeding are widely used. This randomised controlled trial aims to determine whether a policy of early initiation of milk feeds is beneficial compared with late initiation. Optimising neonatal feeding for this group of babies may have long-term health implications and if either of these policies is shown to be beneficial it can be immediately adopted into clinical practice.

**Methods and Design:**

Babies with gestational age below 35 weeks, and with birth weight below 10th centile for gestational age, will be randomly allocated to an "early" or "late" enteral feeding regimen, commencing milk feeds on day 2 and day 6 after birth, respectively. Feeds will be gradually increased over 9-13 days (depending on gestational age) using a schedule derived from those used in hospitals in the Eastern and South Western Regions of England, based on surveys of feeding practice. Primary outcome measures are time to establish full enteral feeding and necrotising enterocolitis; secondary outcomes include sepsis and growth. The target sample size is 400 babies. This sample size is large enough to detect a clinically meaningful difference of 3 days in time to establish full enteral feeds between the two feeding policies, with 90% power and a 5% 2-sided significance level. Initial recruitment period was 24 months, subsequently extended to 38 months.

**Discussion:**

There is limited evidence from randomised controlled trials on which to base decisions regarding feeding policy in high risk preterm infants. This multicentre trial will help to guide clinical practice and may also provide pointers for future research.

**Trial registration:**

Current Controlled Trials ISRCTN: 87351483

## Background

The purpose of this trial is to gain a better understanding of methods of establishing enteral feeding in high-risk preterm infants.

Preterm infants are at increased risk of adverse neonatal outcomes. At particular risk are those infants born after pregnancies in which Doppler studies of umbilical arterial wave forms reveal absent or reversed end diastolic flow velocities (AREDFV) [1]. This phenomenon occurs in approximately 6% of high risk pregnancies [2] and is believed to result from increased placental vascular resistance in response to both acute and chronic hypoxia. Lack of oxygen results in intrauterine growth restriction (IUGR) and the baby is often delivered preterm and small for gestational age. The prognosis is poor compared to those with normal antenatal Doppler studies [1-5]. In infants with abnormal umbilical artery Doppler blood flow velocities it has been shown that blood flow to the head tends to be preserved to support growth of the brain at the expense of blood flow to the abdomen and growth of visceral organs [3,6,7]. In the earlier stages of fetal hypoxia (before AREDFV occurs) the changes of cerebral redistribution may be seen, with widening of the ratio of blood flow velocity in the cerebral artery to that in the umbilical artery - the cerebro-placental ratio. An increase in this ratio has also been associated with increased perinatal morbidity [8-10].

Feeding babies born after AREDFV is a challenge: they are already under-nourished at birth, and good nutrition and growth is essential. However they frequently demonstrate intolerance of milk feeds and have been shown to have an increased incidence of necrotising enterocolitis (NEC) [1,3]. NEC is the commonest serious gastrointestinal emergency in neonatal intensive care units [11] and is associated with a high mortality and morbidity [12,13]. Extreme prematurity is the greatest risk factor, and whilst the specific aetiology is often not clear in individual babies, under perfusion and/or hypoxia of the gut are thought to be important predisposing factors [14]. Enteral feeding and bacterial invasion are commonly associated factors [14,15]. Reduced gut blood flow due to splanchnic vasoconstriction [1,3] may cause hypoxic-ischaemic damage to the intestine or its mucosa predisposing to NEC. Additionally, these conditions may affect normal motor, secretory and mucosal development so that the intestine is more susceptible to stasis, abnormal colonisation and bacterial invasion postnatally. IUGR is associated with bone marrow suppression and neutropenia in early postnatal life, which may also increase susceptibility to infective factors. Babies born after absent EDFV were found to have reduced flow velocities in the coeliac and superior mesenteric arteries compared with birthweight or gestational age matched controls [16]. Flow velocities improved but differences were still apparent on day 7 of life. A subsequent study showed impaired dynamic response in the superior mesenteric artery to the first milk feed in this group [17].

A recent meta-analysis [18] identified 14 observational studies [1,3,5,19-29] comparing the incidence of NEC in infants who had exhibited fetal AREDFV with a group of controls. Nine of these studies show an excess of NEC in the AREDFV infants, with an overall odds ratio for developing NEC of 2.13 (95% CI 1.49-3.03) compared with controls with forward fetal umbilical end-diastolic flow.

The incidence of NEC varies depending on the specific population. In the fourteen studies described above, including a total of 659 infants, the incidence varied between 0-59%, with an average of 12.9%. Among 2681 babies with birthweight 501-1500 grams born in, or transferred to, hospitals participating in the NICHD Neonatal Network between February 1988 and August 1989 the incidence of 'proven NEC' was 10.5%, with 'suspected NEC' at 17.2% [30]. The Vermont Oxford Network LBW Database (infants 401-1500 grams) shows an overall incidence of proven NEC (clinical and radiographic diagnosis) of 6% (VON Annual Reports 2002 and 2003). Analysis of the Network data previously showed an increased risk of NEC in babies with evidence of IUGR (birthweight below 10^th ^centile): OR 1.27 (95% CI 1.05-1.53) [31] but information on antenatal Doppler studies is not collected.

There is no consensus regarding how best to prevent NEC in small, preterm infants. Several strategies of poorly proven efficacy are in use, including delaying feeds, slowly increasing feeds, use of total parenteral nutrition (TPN) and prophylactic antibiotics [32-34]. A systematic review of prophylactic antibiotic use published in the Cochrane Library demonstrated a statistically significant reduction in NEC, but also a significant increase in the incidence of colonisation with resistant bacteria and concluded that there was insufficient evidence to support this approach in clinical practice [35].

The timing of introduction and rate of progression of milk feeds is an area of clinical uncertainty with arguments in favour of both early and late introduction of enteral feeds. Early introduction may improve nutrition and growth, but may increase the risk of NEC [30,32]. Conversely late introduction may be detrimental due to lack of stimulation of the gastrointestinal tract, resulting in villous atrophy and lack of hormone and enzyme production [30,36] and may not reduce the incidence of NEC [37,38]. Prolonged use of parenteral nutrition increases the risks of sepsis, cholestatic jaundice and vitamin and mineral deficiencies [39-41]. IUGR infants are at particularly high risk of parenteral nutrition-related liver disease [42].

The use of minimal enteral nutrition (MEN) (trophic feeds, gut-priming, non-nutritive feeding) has increasingly been used in the early feeding of preterm infants and appears to be well tolerated and beneficial in terms of gut motility, earlier establishment of substantive milk feeding and reduced cholestasis [43-49]. A systematic review published in the Cochrane Library [50] included eight randomised controlled trials and found that infants receiving MEN had an overall reduction in the time taken to achieve full enteral feeding and in the length of hospital stay. Regarding the effect on NEC the reviewers concluded that although no discernable effect was seen an increased risk of NEC could not be excluded - the risk ratio of NEC with MEN was 1.10 (95% CI 0.63-1.90).

Since this review was last updated in 1997, three further trials of MEN have been published. Van Elburg [51] specifically studied babies who were IUGR. Fifty six babies with birthweight below 2000 grams, and below the 10^th ^centile for gestational age, were randomised to receive either MEN (minimal enteral feeds - MEF) starting within 48 hours of birth, or no feeds for the first five days of life (NEF). Among the 42 who completed the trial there was no significant difference between groups in the primary outcome of intestinal permeability using a sugar absorbance test (p = 0.14). There was no difference in secondary outcomes of days to reach full feeds (p = 0.32), days to regain birthweight (p = 0.78) or NEC (0/20 cases in MEF group, 1/22 cases in NEF group (p = 0.76)). In those babies in whom it was measured (25/42), the ratio of umbilical artery to cerebral artery pulsatility index was not predictive of feeding tolerance (p = 0.55). In the two further trials McClure studied 100 infants, seeing 1 and 2 cases of NEC in MEN and control infants respectively [52]. Schanler's trial contained 171 infants, with 13 cases of NEC in the MEN group, compared to 10 cases in the control infants [53]. Combining these results with those of the Tyson meta-analysis, in 692 infants, NEC rates are similar at 10.5% for MEN and 9.4% for control infants (RR 1.07, 95% CI 0.84, 1.36).

The duration of MEN and subsequent rate of advancement is another area of uncertainty. Several studies have suggested that increasing feeds by 30-35 ml/kg/day is as safe as a slower rate of 15-20 ml/kg/day [54,55]. A trial of MEN versus progressive feeding in infants less than 32 weeks gestation was stopped early because of an increased incidence of NEC in the progressive feeding group [56]. In this study however feeds were started late in both groups (mean 10.3 and 9.3 days), and were given as two-hourly infusions followed by 2-hourly fasts. In addition breast milk fortifier was added when feeds of 120 ml/kg/day were reached and doubled when feeding volume reached 140 ml/kg/day.

There is thus no clear evidence to guide the choice of early or late introduction of enteral feeding in high risk IUGR infants. Practice varies widely as was discovered in surveys of neonatal units in two English health regions. In the Southwest enteral feeding was delayed in 9/12 hospitals for IUGR babies of less than 32 weeks gestation ('always' in three, 'usually' in six), and 'usually' in four hospitals for babies at 32-36 weeks. Feeds were delayed for less than five days in five hospitals, greater than five in one hospital and for variable duration in five. Abnormal Dopplers, polycythaemia, presence of umbilical artery catheter and the absence of breast milk made delay more likely. Within the 15 hospitals in the Eastern Region five units commenced feeds on day one, two delayed until day 7, with the remainder commencing feeds between day 2 and 5. The main reason cited for delaying feeds is to try to prevent NEC.

### Aim

We aim to evaluate the effects of an "early" enteral feeding regimen, starting milk feeds on day 2 after birth (between 24 and 48 hours of age) compared to one of "late" introduction of enteral feeds, starting feeds on day 6 after birth (between 120-143 hours of age) in a group of babies identified as being at high risk for NEC and milk intolerance by antenatal Doppler studies.

## Methods and Design

### Ethics Committee Approval

UK Multicentre Research Ethics Committee approval was initially granted in September 2005 with subsequent approvals for protocol amendment; this latest version was approved in January 2008.

### Eligibility and exclusions

#### Hospital eligibility

Hospitals will be eligible to participate in the ADEPT trial providing there are facilities for antenatal Doppler ultrasound of high risk pregnancies and that these are performed with appropriate filter settings, and facilities for neonatal high dependency care including parenteral nutrition.

#### Infant eligibility

Infants admitted to participating neonatal units and satisfying all of the following criteria may be recruited into the study:

1) Gestational age up to and including 34 weeks + 6 days (dated by antenatal ultrasound or clinically).

2) Antenatal ultrasound showing *either*

a) absent or reversed end diastolic flow velocities on at least 50% of the Doppler waveforms from the umbilical artery on at least one occasion during pregnancy

or

b) cerebral redistribution, defined as occurring when both the umbilical artery pulsatility index is greater than the 95^th ^centile and the middle cerebral artery pulsatility index is less that the 5^th ^centile for gestational age [9].

3) Small for gestational age (birth weight < 10^th ^centile for gestational age based on Child Growth Foundation Charts [57]).

4) Postnatal age 20-48 hours

Infants will be excluded if any of the following factors are present:

• major congenital abnormality including known chromosomal abnormality

• twin-twin transfusion

• intra-uterine transfusion or exchange transfusion

• Rhesus iso-immunisation

• significant multi-organ failure prior to trial entry

• inotropic drug support prior to trial entry

• already received any enteral feeding

#### Recruitment and randomisation

Informed written consent for the trial will be obtained from the parents in the first 2 days after birth. This will preferably be in the first 24 hours after birth. The parents will be given a verbal explanation of the study and a written information sheet, and will have an opportunity to discuss participation with the recruiting clinician. If consent is given, and providing no contra-indications occur, the baby should then be randomised between 20 and 48 hours of age. Babies will be randomised to study groups by a central randomisation service, based at the National Perinatal Epidemiology Unit (NPEU), University of Oxford. The randomisation service (website with telephone back-up facility) will request details of the baby and, if eligible, will provide a random allocation to one of the study groups, either "early" or "late" commencement of enteral feeds. The program will use minimisation to ensure balance between the groups with respect to hospital of recruitment, gestational age (< 29 completed weeks or ≥ 29 completed weeks) and type of Doppler abnormality (AREDFV or cerebral redistribution).

### Interventions

Babies will be randomly allocated to an "early" or "late" enteral feeding regimen. These will start milk feeds on day 2 and day 6 after birth, respectively. The regimens for the two groups are based on those currently used in hospitals in the Eastern and South Western Regions, according to a survey of practice carried out in 1999.

The two regimens are as follows:

### 'Early' and 'Late' Feeding Regimens: see Table 1

**Table 1 T1:** 'Early' and 'Late' Feeding Regimens

**Feed regimen**	**'early'**	**'late'**
0-24 hours: day 1	Nil by mouth	Nil by mouth
24-48 hours: day 2	Start milk feeds according to tables 2 & 3	Nil by mouth
48-119 hours: day 3-5	Progress with feeding according to tables 2 & 3	Nil by mouth
120-143 hours: day 6	Progress with feeding according to tables 2 & 3	Start milk feeds according to tables 2 & 3
144 hours onwards - day 7+	Progress with feeding according to tables 2 & 3	Progress with feeding according to tables 2 & 3

For the purposes of the study the choice of milk recommended to mothers to feed their baby should be, in descending order of preference: mother's own breast milk, donated breast milk, infant formula (all dependent on availability). Whether preterm or term formula is the formula given initially will be at the discretion of the local clinician but the recommendation would be for infants with gestation less than 34 weeks to be fed preterm formula within one week of milk commencement. The final choice of which milk is used will rest with the infant's mother. Breast milk fortification may be considered if additional nutritional support is required once the baby is tolerating full milk feeds of breast milk of ≥ 150 ml/kg/day.

The feeding schedule of each group should be followed regardless of the type of milk available, ventilation status, or presence of an UAC unless specifically requested by the local clinician. The decision to withhold feeds or deviate from the feeding schedule in Tables 2 and 3, because of apparent feed intolerance or clinical deterioration, will also remain at the local clinician's discretion. Gastric residuals are not uncommon in preterm infants [58]. Providing the infant is well and has no abnormal abdominal signs it is usually safe to continue with enteral feeds when gastric aspirate is 2-3 ml or less (2 ml in a baby of less than 750 grams birth weight). If feed volumes are withheld or there is any deviation from the schedule in Tables 2 and 3 then the clinician is free to either start again from day 1, re-start at the volume previously tolerated then increase as scheduled daily, or hold for one or more days at a certain volume and then increase as scheduled.

**Table 2 T2:** Feeding schedule - ml/kg/HOUR

**Day of feeding**	**Volume of milk according to birth weight (ml/kg/HOUR)**				
	
	**< 600 g**	**600-749 g**	**750-999 g**	**1000-1249 g**	**≥ 1250 g**
1	0.5	0.5	0.5	0.5	1.0

2	0.5	0.5	0.5	1.0	1.5

3	0.5	1.0	1.0	1.5	2.0

4	1.0	1.5	1.5	2.0	2.5

5	1.5	2.0	2.0	2.5	3.0

6	2.0	2.5	2.5	3.0	3.5

7	2.5	3.0	3.0	3.5	**4.0 - 4.5**

8	3.0	3.5	3.5	**4.0 - 4.5**	**5.0 - 5.5**

9	3.5	4.0	**4.0 - 4.5**	**5.0 - 5.5**	**6.0 - 6.25**

10	4.0	**4.5 - 5.0**	**5.0 - 5.5**	**6.0 - 6.25**	

11	**4.5 - 5.0**	**5.5 - 6.0**	**6.0 - 6.25**		

12	**5.5 - 6.0**	**6.25**			

13	**6.25**				

14	Increase as required				

(NB feed advancement schedule is *the same *for babies in EARLY or LATE groups: only the timing of initiation of feeds differs)

Where 2 numbers are in a cell separated by a hyphen the first number indicates hourly volume/kg to feed for the first 12 hours of each 24 hour period. The second number in each cell indicates hourly volume/kg to feed for the second 12 hours of each 24 hour period.

Feeds should be given hourly or continuously. However, if there are longer intervals between feeds, e.g. 2 hourly feeds, then the milk volume should be increased accordingly.

Light grey background = feeds increase by 0.5 ml/kg every 12 hours.

Dark grey background = feed volume reached 150 ml/kg/day (6.25 ml/kg/hour).

Feeds can be increased as required.

**Table 3 T3:** Feeding schedule - ml/kg/DAY (NB feed advancement schedule is *the same *for babies in EARLY or LATE groups: only the timing of initiation of feeds differs).

**Day of feeding**	**Volume of milk according to birth weight (ml/kg/DAY)**				
	
	**<600 g**	**600-749 g**	**750-999 g**	**1000-1249 g**	**≥ 1250 g**
1	12	12	12	12	24

2	12	12	12	24	36

3	12	24	24	36	48

4	24	36	36	48	60

5	36	48	48	60	72

6	48	60	60	72	84

7	60	72	72	84	**96 - 108**

8	72	84	84	**96 - 108**	**120-132**

9	84	96	**96-108**	**120-132**	**144-150**

10	96	**108-120**	**120-132**	**144-150**	

11	**108-120**	**132-144**	**144-150**		

12	**132-144**	**150**			

13	**150**				

14	Increase as required				

### Other clinical management

Clinical management will include commencement of intravenous parenteral nutrition (glucose, amino acids and intralipid) by the second or third day after birth for all babies. All other aspects of care will be according to local routine practice.

### Outcomes

#### Primary outcome measures

1. Age in days at which full enteral feeding sustained for 72 hours was reached.

2. Necrotising enterocolitis, stage I, II or III [11] (Appendix 1)

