### Data collection

Data will be collected at trial entry, during the infant's stay in the neonatal unit, and at discharge. At trial entry baseline data and eligibility information will be collected and returned to the co-ordinating centre. Information collected during the infant's stay in the neonatal unit will include enteral feeding history (to assess compliance) and other treatments given (to assess whether interventions are used differentially in the two groups). This is important because caregivers will not be blinded to the randomised allocations. Outcome data will be recorded on a form competed by clinicians at discharge. To facilitate later tracing for follow-up and enable notification of any deaths, all infants recruited to the study will be flagged at the NHS Central Register.

All data required for trial analysis will be routinely collected in medical and nursing charts.

Perinatal and early neonatal data will be submitted to the ADEPT Co-ordinating Centre at time of trial entry. Subsequent neonatal data and outcome data will be submitted at discharge *and on transfer to a different neonatal unit if applicable*. Growth data - weight and head circumference - will be collected at 36 weeks post-menstrual age *and *at discharge.

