### Establishment of a blinded endpoint committee

As a result of central monitoring the trial data, it has become clear that the primary end point has not been achieved in a small number of cases. There are two main reasons for this:

i) the introduction of breast-feeding

ii) completion of the feeding log has stopped prematurely in the mistaken belief that the primary endpoint has been reached

Where there is uncertainty as to whether the primary endpoint has been reached, a committee has been established to consider each case and recommend an appropriate course of action. The committee will be blind to allocation.

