## Appendix 1: Modified Bell's criteria from Walsh MC et al 1986

### Stage IA - Suspected NEC

Systemic signs: temperature instability, apnoea, bradycardia, lethargy

Intestinal signs: Elevated pre-gavage residuals, mild abdominal distension, emesis, haem-positive stools

Radiologic signs: Normal or intestinal dilatation, mild ileus

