### Stage IB - Suspected NEC

Systemic signs: Same as stage IA

Intestinal signs: bright red blood from rectum

Radiologic signs: same as stage IA

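### Primary NEC counts suspected (stage I) cases reported by unblinded clinicians, and the blinded committee as described does not cover NEC staging

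*Protocol article*

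**What the plan says.** - **Definition.** Under Primary outcome measures the second outcome is "Necrotising enterocolitis, stage I, II or III [11] (Appendix 1". Stages II-III are not listed as a separate outcome among the primary or secondary measures.
- **Stage I.** Appendix 1 labels it as suspected disease ("Stage IA - Suspected NEC"). The intestinal signs of stage IA are "Elevated pre-gavage residuals, mild abdominal distension, emesis, haem-positive stools" and its radiology is "Normal or intestinal dilatation, mild ileus". Stage IB adds "bright red blood from rectum" with the same radiology. Pneumatosis first appears at stage IIA.
- **Residuals.** The feeding regimen text under Interventions says: "Gastric residuals are not uncommon in preterm infants".
- **Blinding.** Data collection explains why co-treatments are recorded: "This is important because caregivers will not be blinded to the randomised allocations". The same section has clinicians complete the outcome form at discharge.
- **Committee.** "Where there is uncertainty as to whether the primary endpoint has been reached, a committee has been established". It works blind to allocation. The two reasons given for it are breast-feeding and a feeding log stopped too early.
- **Power.** Sample size takes NEC at about 15% and a fall to 7.5%, with 60% power at 400 babies. It does not say which stages the 15% covers. Background reports one cohort with proven NEC at 10.5% and suspected NEC at 17.2%, as separate figures.

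**The concern.** Three features meet in one primary outcome: a soft lowest category, assessors who know the allocation, and an intervention that bears on some of the signs. Pre-gavage residuals, and largely emesis, appear only in a baby who is being fed, and the arms start feeds about four days apart. A clinician deciding whether a distended baby with residuals has suspected NEC or ordinary feed intolerance knows which policy the baby is on. The committee that could remove that influence is described for the feeding endpoint only.

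Two different problems could follow. The first is detection bias: stage I is recorded more readily in one arm with no difference in disease. The second is dilution: stage I events that do not respond to allocation add equally to both arms and pull the relative risk towards 1. NEC is kept as a primary outcome for its clinical importance, so the result will be read as evidence on safety in either direction.

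**Working it through.** **1. The plan's own figure.** Inputs from Sample size: 15%, 7.5%, 400 babies (200 per arm). The two-sided 5% level is stated in the Abstract for the feeding outcome and assumed here for NEC.

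Power = Φ[(d − 1.96·SE0)/SE1], where d = p1 − p2, SE0 = √(2·p̄(1−p̄)/n) and SE1 = √((p1(1−p1) + p2(1−p2))/n).

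For 15% v 7.5%: SE0 = √(2 × 0.1125 × 0.8875/200) = 0.0316; SE1 = √((0.1275 + 0.0694)/200) = 0.0314; (0.075 − 0.0619)/0.0314 = 0.417; power 66%.

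With continuity correction, n is replaced by n(1 − 1/(nd))² = 200 × (1 − 1/15)² = 174, and power is 60%. This matches the stated figure; Fisher's exact test gives 61%. The arithmetic is sound. It assumes that the whole outcome, all stages together, halves.

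**2. Dilution, if stage I does not respond to allocation.** Assumption: 5 of the 15 points are stage I and equal in both arms, and stage II-III halves from 10% to 5%. All stages are then 15% v 5 + 5 = 10%.

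- 15% v 10%: SE0 = 0.0331, SE1 = 0.0330; (0.05 − 0.0648)/0.0330 = −0.449; power 33%.
- 10% v 5%: SE0 = 0.0263, SE1 = 0.0262; (0.05 − 0.0516)/0.0262 = −0.062; power 48%.

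The corrected column below uses the substitution in step 1; for d = 0.05 it gives 200 × 0.9² = 162.

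| Contrast, 200 per arm | Uncorrected | Continuity-corrected |
|---|---|---|
| All stages as planned, 15% v 7.5% | 66% | 60% |
| All stages, 5 points unaffected, 15% v 10% | 33% | 27% |
| Stage II-III alone, 10% v 5% | 48% | 40% |

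**3. Range for the stage I share.** The protocol gives no share for this population. The cohort in Background, selected by birthweight, gives 17.2/(10.5 + 17.2) = 62% if suspected and proven are exclusive, or (17.2 − 10.5)/17.2 = 39% if suspected includes proven. Uncorrected power, with stage I unaffected and stage II-III halved:

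| Stage I share of 15% | All stages | Power | Stage II-III | Power |
|---|---|---|---|---|
| 40% | 15% v 10.5% | 27% | 9% v 4.5% | 43% |
| 60% | 15% v 12% | 14% | 6% v 3% | 30% |

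**4. The reverse case.** If stage I halves along with stage II-III, all stages are 15% v 7.5% (66%) and stage II-III alone is 10% v 5% (48%). Including stage I then gains 18 points of power.

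**5. Detection bias, illustrated.** Assume no true difference, 15% in one arm, and extra stage I recorded in the other. The excess is invented; nothing in the protocol gives its size. The chance of a significant result in the direction of the excess is 2.5% without bias.

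| Extra points | Relative risk | Chance of significance |
|---|---|---|
| 2 | 17/15 = 1.13 | 8% |
| 3 | 18/15 = 1.20 | 12% |
| 4 | 19/15 = 1.27 | 19% |
| 6 | 21/15 = 1.40 | 34% |

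**The case against.** **Late babies cannot show the sign.** A reader might infer that babies who are unfed on days 2-5 are protected by definition, so that stage I must be over-called in the Early arm. The protocol does not support that. The outcome has no day 2-5 window, and the form is completed at discharge. The advancement schedule is the same in both arms, so a Late baby passes through the same feeding days about four days later. Only residuals, and largely emesis, need feeding; apnoea, bradycardia, temperature instability, distension and rectal blood do not. Appendix 1 lists systemic, intestinal and radiologic signs together and does not say that residuals alone make stage IA.

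**Clinicians lean one way.** Background says that preventing NEC is the main reason given for delaying feeds. It also reports mixed practice: in the Eastern Region five of 15 units fed on day one and two waited until day 7, while in the South West 9 of 12 delayed for growth-restricted babies below 32 weeks. A uniform direction of belief is not shown.

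**A condensed article.** Review of NEC cases and analysis by stage may be set out in the full protocol or the analysis plan, and the article does not say who assigns the stage. This stands as a caution. But the primary definition, the unblinded setting and the two reasons for the committee are stated here. An analysis by stage would address dilution, but not staging done with the allocation known.

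**Stage I belongs in the outcome.** The Aim concerns babies at risk of NEC and milk intolerance, the Sample size section admits limited power, and perforation, gastrointestinal surgery and death are listed as harder secondary outcomes. This also stands: dropping stage I from the primary is a trade-off, and step 4 shows that it can lose power.

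**Conclusion.** The concern holds in a limited form. A primary outcome that includes suspected NEC, reported in an unblinded trial with no described blinded staging, is open to detection bias of unknown size and unproven direction. Dilution is conditional. With 5 of 15 points unaffected by allocation and stage II-III halved, power is 33% for all stages against 48% for stage II-III (27% and 40% with continuity correction). With stage I shares of 40-60% it is 27-14% against 43-30%. If stage I responds equally, counting it helps.

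Two stronger conclusions do not follow. The stated 60% is not an error: it reproduces with continuity correction and should be compared only with corrected figures. Nor do the documents show that stage II-III ought to replace the primary definition. This is a low-cost improvement to how a primary outcome is ascertained, not a flaw that invalidates the design.

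**What to change.** 1. Keep stage I-III as the primary NEC definition.
2. Extend the existing blinded committee's remit to assign the stage of every reported NEC case, from films and a clinical summary with allocation and feed-start dates removed.
3. Pre-specify stage II-III NEC as a key secondary outcome, to be read alongside the primary before an NEC effect is claimed.
4. State in Sample size which stages the 15% covers, and give the power for stage II-III on the same basis as the 60%.

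Cost: a wording change and about 400 × 0.15 = 60 case reviews by a committee that already exists, or 30 + 15 = 45 if NEC halves in one arm. Power for stage II-III will be low, about 40% with continuity correction for 10% v 5%, and should be stated openly. Central staging covers only cases that sites report, so it reduces bias in classification but not bias in which babies come under suspicion. The stage II-III outcome, which needs radiological change, helps with the latter.
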